# Single-centre, single-blinded, randomised, parallel group, feasibility study protocol investigating if mandibular advancement device treatment for obstructive sleep apnoea can reduce nocturnal gastro-oesophageal reflux (MAD-Reflux trial)

**DOI:** 10.1136/bmjopen-2023-076661

**Published:** 2023-08-24

**Keywords:** Health economics, SLEEP MEDICINE, GASTROENTEROLOGY, Feasibility Studies, ORAL MEDICINE

## Abstract

**Introduction:**

Just under half of patients with obstructive sleep apnoea (OSA) also have gastro-oesophageal reflux disease (GORD). These conditions appear to be inter-related and continual positive airway pressure (CPAP) therapy, the gold standard treatment for OSA to prevent airway collapse, has been shown to reduce GORD. As the impact of mandibular advancement devices, a second-line therapy for OSA, on GORD has yet to be investigated, a feasibility study is needed prior to a definitive trial.

**Methods:**

This will be a single-centre, single-blinded, tertiary-care based, interdisciplinary, parallel randomised controlled study. Potential OSA participants presenting to the sleep department will be pre-screened for GORD using validated questionnaires, consented and invited to receive simultaneous home sleep and oesophageal pH monitoring. Those with confirmed OSA and GORD (n=44) will be randomly allocated to receive either CPAP (n=22) or MAD therapy (n=22). Following successful titration and 3 weeks customisation period, participants will repeat the simultaneous sleep and oesophageal pH monitoring while wearing the device. The number of patients screened for recruitment, drop-out rates, patient feedback of the study protocol, costs of interventions and clinical information to inform a definitive study design will be investigated.

**Ethics and dissemination:**

Health Research Authority approval has been obtained from the Nottingham 2 Research Ethics Committee, ref:22/EM/0157 and the trial has been registered on ISRCTN (https://doi.org/10.1186/ISRCTN16013232). Definitive findings about the feasibility of doing 24 hour pH oesophageal monitoring while doing a home sleep study will be disseminated via clinical and research networks facilitating valuable insights into the simultaneous management of both conditions.

**Trial registration number:**

ISRCTN Reg No: 16013232.

STRENGTHS AND LIMITATIONS OF THIS STUDYThis feasibility protocol is designed to gauge patient recruitment, acceptability and signal clinical efficacy for a definitive power calculation.The clinical trial is interdisciplinary involving dental, sleep and gastroenterology clinicians alongside patients, health psychologists, health economists and statisticians.Feasibility for health economic outcomes is also being assessed.Findings will inform a definitive trial rather than a clinical outcome.

## Introduction

One billion people worldwide and 8 million people in the UK (24.5% of the population) are estimated to have obstructive sleep apnoea (OSA).^1^ It is the most common sleep disorder, characterised by frequent pauses in breathing (apnoeas and hypopnoeas) during sleep due to airway blockage caused by intermittent relaxation of the throat muscles. Sleep becomes broken, so in the daytime patients reported of sleepiness, fatigue and have other symptoms such as difficulty concentrating, memory impairment, feeling irritable and depressed.^2^ Their own and their bed partner’s quality of life is reduced.^2^ Patients are at a higher risk of type 2 diabetes, high blood pressure, heart disease, strokes and dying of all causes compared with people without OSA. This risk increases with OSA severity; with severe OSA, the risk of cardiac events and strokes is doubled and of cardiac death is tripled.^3^ People with untreated OSA also put the public in danger as they have more road traffic accidents than people without OSA and compared with themselves once on treatment.^4 5^ The societal level-costs of undiagnosed OSA in the USA alone amounted to over $150 billion per year.^6^ In Italy, OSA causes an economic burden ranging from €10.7 to €32 billion per year.^7^

Gastro-oesophageal reflux disease (GORD), defined by the montreal consensus as ‘a condition that develops when the reflux of stomach contents causes troublesome symptoms and/or complications’ with oesophageal/typical and extraoesophageal/atypical symptoms,^8^ is also common in the UK. There is a strong association between OSA and GORD, partly due to common risk factors such as obesity, high alcohol consumption and diet and also due to the impact that apnoeic events have on the lower oesophageal sphincter (LOS).^9^ A recent meta-analysis estimated that 45.2% of OSA patients had episodes of extra-oesophageal reflux independent of BMI.^9^ Around 40–81% of patients suffering from GORD report that their symptoms occur during sleep.^10^ There is a growing body of evidence that ontinuous positive airway pressure (CPAP) therapy, the gold-standard therapy for OSA,^11^ can reduce levels of gastro-oesophageal disease^12–15^ by maintaining a patent airway, thus reducing intrathoracic pressure differentials. CPAP therapy increases the baseline LOS barrier pressure during sphincter relaxation and decreases the duration of sphincter relaxation.^16^ Mandibular advancement devices (MADs), a second line therapy, also maintain a patent airway, which may also have a similar impact on intrathoracic pressure differentials and duration of LOS relaxation. In addition, the greater compliance observed with MADs may mean that reflux is suppressed for a greater proportion of the night.^17^ However, both theories remain untested to date. We do not have sufficient data to gauge an effect size for a definitive powered trial. We do not know if patients are willing to wear multiple devices and tests while trying to sleep and whether acceptability will influence the data. We are also unaware of the most appropriate quality of life measure to accurately assess patient impact and health economics. Therefore, a feasibility trial is needed prior to a definitive evaluation.

From an NHS perspective, CPAP and MADs are both cost-effective treatments.^18^ CPAP therapy has been shown to generate an incremental cost-effectiveness ratio below £5000 per quality-adjusted life year (QALY) gained.^19^ Using CPAP over a period of 14 years resulted in saving National Health Service (NHS) costs (nearly £1000 per patient) and generated health benefits for people with OSA, for example, reduction in stroke risk and road traffic accidents.^20^

In the UK, the yearly medication costs of GORD treatment are around £200 million for histamine receptor antagonists and £300 million for proton pump inhibitors (PPIs).^21^ The cost implication of the impact of CPAP therapy or MAD therapy on GORD has yet to be evaluated.

The overall aim of this project is to conduct a feasibility study to assess patient recruitment and tolerance of the trial. The secondary aims are to calculate an estimate of the primary outcome effect to determine the sample size needed for the definitive trial if the progression criteria are met, to determine the optimum measure of quality-of-life impact for this patient cohort.

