##### Primary clinical outcome to signal efficacy and inform a definitive power calculation

Change in percentage acid contact time pH <4 with the device in situ measured using nocturnal data from 24-hour pH monitoring at initial gastroenterology screening visit and follow-up gastroenterology assessment post-therapy.

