### Sample size

There are several studies investigating change in per cent acid exposure from baseline while wearing the CPAP device. Sample sizes suggested from current data based on change in total acid were between 86 to 168 per group (excluding any attrition).^12 39^ Using the smallest effect size published (Tawk *et al*^12^), assuming a one-sided non-inferiority design with a margin of 4.15 (per cent total acid) together with an SD of 10.8 with a power of 90% and alpha of 2.5% for a definitive study, this would require a sample of 288 (without attrition). Considering the likelihood of the main study finding an effect of this size within a 80% CI, then an approach taken by Cocks and Torgerson^40^ requires a feasibility sample equivalent to approximately 9% of the proposed definitive sample requiring 26 participants. Accommodating an overall attrition rate, including tolerance to the devices, of 40% requires a sample of 44 to be randomised. A sample of 44 will also give us a 95% CI of +/−14% around the attrition rate.

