### Statistical analysis

Baseline characteristics will be summarised for all participants within the trial arms.

The feasibility outcomes include:

Percentage of screened patients who were eligible for the trial.Percentage of eligible patients who agreed to participate.Percentage of patients who completed the trial.

We will then assess one clinical outcome to assess signal of efficacy, which is the change in percentage acid contact time pH <4 with the device in situ. Participants’ uptake of and adherence to both CPAP and MAD, as well as follow-up rates, will be summarised and presented as percentages. Although determining differences in clinical outcomes between the arms is not the primary purpose of this feasibility study, comparisons will be undertaken to investigate the feasibility of studying these outcomes and to calculate potential estimates and 95% CIs. As recommended in guidelines for good practice for the analysis of pilot studies,^41^ the focus of the results will be on the estimates of the treatments rather than statistical significance and as such no hypothesis testing will be undertaken. Differences between the two comparison groups will be presented in the form of an unadjusted mean difference for continuous outcomes, and an OR for binary outcomes, with their associated 95% CIs. These comparisons will be made on an intention to treat basis with consideration given to per protocol analysis as sensitivity. While every effort will be made to minimise missing data, assessment of the levels of missing data will indicate suitability of measures to be continued into the definitive trial.

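### The aims let the pilot's own effect estimate determine the definitive sample size, but 26 completers cannot estimate that effect precisely enough

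*Protocol article*

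**What the plan says.** The last paragraph of the Introduction lists among the secondary aims "to calculate an estimate of the primary outcome effect to determine the sample size needed for the definitive trial", provided that the progression criteria are met. The outcomes section heads the acid contact time measure "Primary clinical outcome to signal efficacy and inform a definitive power calculation", and the strengths and limitations box says much the same.

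The Sample size section assumes a one-sided non-inferiority design with a margin of 4.15 percentage points of total acid, "together with an SD of 10.8 with a power of 90% and alpha of 2.5% for a definitive study". It arrives at 288 without attrition, takes about 9% of that (26 participants) for the feasibility sample, and allows 40% attrition to reach 44 randomised.

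The Statistical analysis section plans unadjusted mean differences between arms "to calculate potential estimates and 95% CIs", with the emphasis on estimation and no hypothesis tests.

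**The concern.** A non-inferiority trial is sized from a margin set in advance, an SD and an assumed true difference, usually 0. The aim as worded puts the pilot's estimated effect in the deciding role. A trial of this size estimates that effect with an error as large as the margin, so the definitive size would be driven largely by chance. A lucky pilot result would produce a trial that is too small. An unlucky one would produce a very large trial or none. The SD, the correlation and the completion rates are what a pilot of this size can usefully supply, and the aim does not mention them.

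**Working it through.** **Inputs.** From the Sample size section: margin 4.15, SD 10.8, power 90%, one-sided alpha 2.5%, 26 completers. Assumed: 13 completers per arm, SD 10.8 applying to the change in each arm, and a true difference of 0. A positive difference d means that MAD does worse than CPAP.

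**The plan's own figures.** n per arm = 2 × [10.8 × (1.960 + 1.282) / 4.15]² = 142.3, so 143 per arm and 286 in total, against 288 stated. Then 0.09 × 288 = 25.9, so 26, and 26 / 0.6 = 43.3, so 44. The chain reproduces, and it does so at d = 0.

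**Precision of the pilot difference.**
- SE = 10.8 × √(2/13) = 4.24, already larger than the margin.
- 95% half-width = 2.064 × 4.24 = 8.74, about 2.1 times the margin.
- With all 44 analysed: SE = 10.8 × √(2/22) = 3.26 and 95% half-width 6.57.

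**Entering the observed difference as the true one.** n per arm = 2 × [10.8 × 3.2415 / (4.15 − d)]².

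| Observed d | Definitive total |
|---|---|
| −4.24 (−1 SE) | 70 |
| −2 | 130 |
| −1 | 186 |
| 0 | 286 |
| +1 | 496 |
| +2 | 1,062 |
| +3 | 3,708 |
| +4.15 or more | none exists |

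True power at a true difference of 0 is Φ[4.15 / (10.8 × √(2/n)) − 1.960]. For d = −2, n = 65 per arm, and power = Φ(2.191 − 1.960) = 59%.

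**How often this goes wrong if the truth is 0.**
- No feasible size: P(d ≥ 4.15) = 1 − Φ(4.15 / 4.24) = 16%. With all 44 analysed it is still about 10%.
- True power below 70%: this needs fewer than 2 × [10.8 × (1.960 + 0.524) / 4.15]² = 83.6, that is 84 per arm. With the SD taken as known, that happens when d < −4.15 × (3.2415 / 2.4844 − 1) = −1.26, with probability Φ(−1.265 / 4.236) = 38%. Simulating 400,000 pilots with the SD also estimated gives about 39%. Both are shares of all pilots and come on top of the 16%.

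**Sizing on the pilot SD alone, with d set to 0.** Power falls below 70% only if the pilot SD is under 10.8 × 2.4844 / 3.2415 = 8.28. That is P(χ² on 24 df < 24 × (8.28 / 10.8)²) = about 6%. Using the upper one-sided 80% limit of the SD (multiplier 1.153) brings it below 1%.

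**The case against.** The strongest reply is that no section says the observed MAD–CPAP difference will be entered as the true difference. The outcomes heading speaks only of signalling and informing, and the effect could mean the change within each arm. That is fair, so the percentages above are conditional on the plug-in reading. It does not rescue the wording. The aim says the estimate is there to determine the size, and nothing in the article says that the SD will be used instead. The within-arm reading has the same weakness: 13 in an arm give an SE of 10.8 / √13 = 3.00 and a 95% half-width of 2.179 × 3.00 = 6.5.

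It is also true that the only sizing calculation shown already uses a margin, an SD and, in effect, a difference of 0. The defect is therefore one of wording in the aims, which should be brought into line with the Sample size section.

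Four stronger readings are tempting, and the document does not support them:

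- **A wrong go/no-go decision.** Sizing is conditional on progression criteria, and the primary outcomes concern screening, randomisation and completion. Nothing makes the effect estimate a progression criterion.
- **The 95% CIs are an error because the sample was justified at 80%.** Reporting 95% CIs in an estimation-only pilot is sound, and excluding the margin is not planned.
- **The 80% CI must be a one-sided limit.** This is an inference about a cited method. At the stated 90% power a one-sided 80% limit gives (0.842 / 3.2415)² = 6.7% of the definitive size, not 9%.
- **The margin is the entire CPAP effect, so an ineffective MAD would pass.** The text introduces the margin after "Using the smallest effect size published", but whether 4.15 is all or part of that effect cannot be settled from the article.

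**Conclusion.** The point holds in a limited form. As written, the aim assigns the pilot's effect estimate a task that 26 completers cannot perform with usable precision: the SE is 4.24 against a margin of 4.15, and the 95% CI is about ±8.7. If the observed between-arm difference were plugged in and the truth is 0, about 16% of pilots would give no feasible size and about 38–39% a definitive trial with true power under 70%. Sizing on the SD alone gives about 6%. These figures rest on a 13/13 split, an SD of 10.8 for change in each arm, and the plug-in reading of the aim. The imprecision does not depend on that reading, and full retention does not remove it. The point concerns a secondary aim. The feasibility outcomes, the number randomised and the descriptive analysis all stand, so it is worth correcting before analysis but is not a serious fault in the trial.

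**What to change.** In the aims at the end of the Introduction and under the primary clinical outcome heading, with the strengths and limitations box to match, replace sizing from the estimated effect with a statement to this effect: the definitive sample size will use a non-inferiority margin fixed beforehand on external or clinical grounds and an assumed true difference of 0; from this trial it will take only the SD of the acid contact time measure with an upper confidence limit, the baseline–follow-up correlation and the completion rates. State that the between-arm estimate and its 95% CI are descriptive. The Statistical analysis section needs no new criterion.

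As an optional clarification in the Sample size section, say what the 80% CI refers to in "Considering the likelihood of the main study finding an effect of this size within a 80% CI", and whether 4.15 is all or part of the published CPAP effect.

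The cost is wording only, with no extra participants or data. The definitive size may come out larger. For example, if the pilot SD were exactly 10.8, its upper one-sided 80% limit would be 10.8 × 1.153 = 12.45, and the total would rise from 286 to about 286 × 1.33 = 380.

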## Methods and analysis

### Study design

This will be a single-centre, single-blinded, tertiary care-based, interdisciplinary parallel 1:1 randomised controlled study. The trial has been registered on ISRCTN (https://doi.org/10.1186/ISRCTN16013232).

### Setting

Participants will be recruited from King’s Health Partners sleep services at Guy’s and St Thomas’s Foundation Trust (GSTT, London, UK).

#### Outcomes

##### Primary outcome measures

Percentage of approached patients who were screened for the trial measured using the percentage of patients eligible of those screened at ay 2 of the screening visit.Percentage of eligible patients who were randomised measured using the percentage of screened patients who met the eligibility criteria versus those who were randomised at the randomisation timepoint.Percentage of patients who completed the trial measured using number of patients who were randomised versus those who completed the trial at Day 2 of the final visit.

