### Study screening procedures

Following written informed consent by a trained member of the research team, participants will undergo assessments at a screening visit to ensure eligibility is met. Participants will be informed that PPIs will need to be stopped 7 days prior and H2-receptor antagonists or antacids 48 hours prior to this visit. Participants will complete an RSI questionnaire, ESS questionnaire, Leicester Cough Questionnaire and several QoL questionnaires. A full dental examination will be conducted to ensure that participants are dentally fit to wear an MAD if allocated to this intervention. For the gastroenterology assessment, the patient will initially need to undergo high-resolution manometry (HRM). Following local analgesia of the nares the catheter will be introduced transnasally and the patient instructed to drink water through a straw while the HRM catheter is advanced to the stomach. The HRM catheter depth will be adjusted to ensure manometric visual of the upper oesophageal sphincter, the gastro-oesophageal junction and gastric pressures. Ten single swallows of 5 mL will be performed with each being 20 s apart. Each 5 mL water swallow will be assessed in accordance with Chicago classification (V.3) using Manoview software (V.3) (Sierra Scientific Instruments). The HRM catheter will then be removed.

Patients will then undergo reflux monitoring using Sandhill Scientific multichannel impedance pH catheters (ZANBG-44), which are inserted transnasally after applying local anaesthesia (xylocaine). The dual pH sensors of the catheter will be positioned 5 cm below and above the manometric LOS. The impedance sensors will be positioned above the LOS by 3 cm, 5 cm, 9 cm, 15 cm and 19 cm. The data will be captured by ZepHrTM recording device.

For the 24 hours while the probe is inserted, the participant will be asked to complete a food diary as food and drink will impact on their reflux. Stopping reflux medication and the food diary are part of standard care for this procedure.

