## Discussion

Given the increasing prevalence of both OSA and GORD, it is important to further investigate the inter-relationship between the conditions and the impact of OSA treatment on GORD. While there is evidence that CPAP reduces GORD, the effect size is unclear, and the impact of MADs on GORD is entirely un-investigated.

This feasibility trial is designed as a first step to provide this important information for patients deciding on treatment choices and the prescribing sleep clinician. This trial will give us insights into the feasibility for testing patients, patient experience, the mechanism of action and the overall effect. There were several items for consideration when developing the study design. First, we chose to use a level 2 sleep study rather than polysomnography. This was because a level 2 device is sufficient for diagnosis of OSAS provided no other respiratory/sleep pathologies are suspected. At the time of recruitment, all participants had been assessed by their managing consultant and diagnosed as having suspect OSAS. The primary outcome of this study is a gastroenterology outcome and AHI is used solely as the inclusion criteria. Furthermore, the final assessment night for the patient will necessitate them to wear a sleep study device, a nasal pH monitor and their MAD or CPAP therapeutic intervention. We thought this would be easier for the patient if done at home. Finally, we would like the definitive trial to be a multicentre trial. Not all centres will have capacity for polysomnography. For these reasons, we deemed that a Watch-PAT was appropriate. We have also considered items such as the interference of the nasal catheter with the CPAP mask. This has been extensively discussed with our PPI group, some of whom have already undergone 24-hour pH monitoring while wearing their CPAP. The mask seal can be maintained with strategic placement of the nasal catheter and tape. There is also precedent for this in previous studies.^12 16^ However, the feasibility of this will be explored.

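### Primary feasibility outcome 1 is named as screened among approached but measured as eligible among screened, outcome 2 changes between sections, and no stated measure covers uptake from approach to screening

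*Protocol article*

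**What the plan says.** The Primary outcome measures section gives three proportions, each with a name, a measure and a timepoint.

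- Outcome 1: "Percentage of approached patients who were screened for the trial measured using the percentage of patients eligible of those screened", taken at day 2 of the screening visit.
- Outcome 2: "Percentage of eligible patients who were randomised measured using the percentage of screened patients who met the eligibility criteria versus those who were randomised", taken at randomisation.
- Outcome 3: "Percentage of patients who completed the trial measured using number of patients who were randomised versus those who completed the trial", taken at day 2 of the final visit.

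The Statistical analysis section gives its own list: "Percentage of screened patients who were eligible for the trial", then "Percentage of eligible patients who agreed to participate", then the percentage completing the trial.

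On the order of events, Study screening procedures states: "Following written informed consent by a trained member of the research team, participants will undergo assessments at a screening visit". Those assessments include the dental examination, manometry, pH monitoring and home sleep study that decide eligibility. The end of the Introduction gives the overall aim as assessing recruitment and tolerance of the trial.

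**The concern.** Outcome 1 carries the measure of another proportion. Screened/approached describes how many people accept the invitation to be tested. Eligible/screened describes how many of those tested meet the criteria, which is a diagnostic yield. The second gives no information about the first. Since the analysis list also uses the second, the proportion that outcome 1 names has no stated measure and no stated analysis.

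Outcome 2 names a different event in each section. Randomisation is a recorded event after eligibility is known. Agreeing to participate could be the written consent given before eligibility testing, a later agreement to be randomised, or a response to the first approach.

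Recruitment rates are a main product of this study, and the Introduction says that going on to a definitive trial depends on progression criteria. A team planning that trial needs to know how many patients to approach. As written, the report could give the yield from screening onwards and leave out the step before it, where patients decide whether to accept the catheter and the sleep study. The Introduction shows that this kind of willingness is an open question: "We do not know if patients are willing to wear multiple devices and tests while trying to sleep".

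**Working it through.** **1. The plan's own figures.** These are checked first to show that they do not depend on the outcome definitions. All inputs are from the Sample size section.

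- Definitive trial: margin 4.15, SD 10.8, power 90%, one-sided alpha 2.5%, true difference taken as 0. Per arm, n = 2 × (1.96 + 1.2816)² × 10.8² / 4.15² = 142.3, so 143, or 286 in total. About one more per arm for the t-distribution gives the stated 288.
- Feasibility size: 0.09 × 288 = 25.9, so 26. Allowing for 40% attrition, 26 / 0.6 = 43.3, so 44.
- Precision around attrition: 1.96 × √(0.4 × 0.6 / 44) = 0.145, or 14.5 points, against the stated 14.

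These figures reproduce. The only stated precision concerns attrition, which is the complement of outcome 3. None concerns outcomes 1 or 2.

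**2. The definitions side by side.**

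| Outcome | Name (Primary outcome measures) | Measure (Primary outcome measures) | Statistical analysis |
|---|---|---|---|
| 1 | screened / approached | eligible / screened | eligible / screened |
| 2 | randomised / eligible | randomised / eligible (loosely worded) | agreed / eligible |
| 3 | completed | completed / randomised | completed (denominator not restated) |

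One name of three conflicts with its own measure (outcome 1). Two of three differ between sections: outcome 1 by its name and outcome 2 by its numerator. Outcome 3 has no conflict. The timepoint for outcome 1, day 2 of the screening visit, is when the monitoring ends and eligibility can be judged, so it fits the measure and not the name.

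**3. Whether another item supplies the missing proportion.**

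- Secondary outcome measures: the number of potential participants identified, with and without screening of referral letters. This is a count by route. Being identified is not the same as being approached.
- Abstract, Methods: the number screened, with no approached denominator.
- Qualitative interviews: people who chose not to take part are sampled for their reasons. No rate comes from this.

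None is screened/approached.

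**4. Illustration of what the missing step can do.** The rates here are assumptions; the article gives none. Take 50% of screened patients eligible and 80% of eligible patients randomised. Reaching 44 randomised needs 44 / (0.5 × 0.8) = 110 screened. With uptake u, the number approached is 110 / u, and the 95% half-width for u is 1.96 × √(u(1 − u) / approached).

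| Assumed uptake | Approached | Half-width (points) | Eligible/screened as reported |
|---|---|---|---|
| 20% | 550 | 3.3 | 50% |
| 40% | 275 | 5.8 | 50% |
| 60% | 183 | 7.1 | 50% |
| 80% | 138 | 6.7 | 50% |

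The last column is the same in every row while the number approached varies fourfold. With eligibility from 30% to 70% as well, the ranges are 79 to 183 screened and 98 to 917 approached, with half-widths for uptake of 2.6 to 8.4 points. The proportion could therefore be estimated with useful precision if approaches are counted.

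**The case against.** The best defence is that this is a slip of wording in a condensed article. Screened/approached is named as a primary outcome, so the intention is visible. Figure 1 is captioned as showing the feasibility outcomes but is not available here, and the full protocol, which the article says is accessible through the registry, has not been seen. The heaviest burden, with sleep device, catheter and therapy worn together, falls on the final assessment night, and completed/randomised captures tolerance of that. No sample size, allocation or clinical analysis is affected.

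Much of this stands and limits the point. Four stronger readings are tempting, and the article does not support them.

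- A reader might infer that all three primary outcomes are wrongly defined. Outcome 3 is consistent, and outcome 2 is coherent where it is first defined.
- A reader might infer that agreement among eligible patients must be close to 100% because they have already consented. The Qualitative interviews section expects eligible, screened patients who do not take part, and the phrase may simply mean agreeing to randomisation. It is ambiguous, but not shown to be uninformative.
- A reader might infer that uptake will never be estimated, or that it is the main recruitment unknown. The text supports only that no stated measure or analysis estimates it. Nothing in the article ranks it above the other steps.
- A reader might take "The primary outcome of this study is a gastroenterology outcome" in the Discussion as a rival primary outcome. That sentence explains the choice of sleep device, and the Outcomes section separates the feasibility outcomes from the primary clinical outcome. It is minor wording.

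What the defence cannot remove is the conflict within outcome 1. Neither a figure nor a fuller document changes the fact that this text gives one proportion as the measure of another, or that the analysis list omits the one named.

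**Conclusion.** The point holds in this form: outcome 1 is mismeasured against its own name, outcome 2 has two different numerators, outcome 3 is sound, and uptake from approach to screening has no stated measure or analysis in a study whose overall aim includes recruitment. This contradiction in a primary outcome should be resolved before the feasibility results are reported.

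The conclusion rests on the text alone and needs no assumed rate. The size is one internal conflict in three outcomes, two differences between sections in three, and no change to 288, 26, 44 or the stated interval. The figures for numbers approached rest on assumed rates. They show that the unmeasured step can matter; they do not show by how much it will. Nor do they show that the plan overstates yield: a rate per screened patient is correct as such, and would mislead only if someone read it as a rate per approached patient, which the article does not propose.

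**What to change.** Use one list, worded identically under Primary outcome measures and Statistical analysis, with a numerator, denominator and timepoint for each item:

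1. Consented and screened / approached.
2. Eligible / screened, at day 2 of the screening visit.
3. Randomised / eligible, at randomisation.
4. Completed day 2 of the final visit / randomised.

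State what counts as approached. Participants and recruitment describes both a first conversation with the direct care team and a later invitation with the information sheet, and either could serve if it is used consistently. Replace the wording about agreeing to participate with randomised, or define the event it means and when it occurs.

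The cost is a wording change and one added requirement: the recruitment log must record the number approached. That count should be kept from the start because it is hard to recover after recruitment closes. No visit, test or participant is added, and the sample size stands.
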